## 2. Methods

### 2.1. Study Design

The study is a single-blind, cluster-RCT study, with the kindergarten class as the cluster for the intervention. This study is a part of the Physical Exercise on FMSs and PF of preschoolers (PEFP) project. The PEFP project is a series of studies, including a cross-sectional survey (covering six provincial and municipal regions in China) and the aforementioned RCT (implemented in Putuo District, Shanghai, China). Preschoolers recruited from 5 kindergartens will be cluster-randomly allocated to 5 groups (i.e., four intervention groups and one control group). The intervention groups are (1) the BG group, consisting of football, basketball games, etc.; (2) the RA group, including cheerleading, rhythm exercise, etc.; (3) the BM group, consisting of different basic movements, such as walking, running, jumping, climbing, throwing, catching, etc.; and (4) the MA group, combination of all kinds of physical exercise that have been used in other intervention studies. The control group (control) is an unorganized PA group (Figure 1). The content of the intervention comes from previous research combined with consultation and interviews with preschool educators [7,37].

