### 2.3. Randomization and Masking

First, the information of the recruited kindergarten will be obtained, including the name of classes, and the number of children in each class. Then, an opaque envelope will be used for simple random assignment, and recruited kindergartens as a unit will be randomly assigned to one of five groups. The generation of the random assignment will be completed by the main person who is in charge of the intervention. As this is a behavioral and skill-specific intervention, eligible children in the same class will receive an identical strategy to avoid confounding influences, such as different exercise instruments or teachers. Furthermore, details of the intervention group allocation will not be available to participants and their teachers. Data analysts will not include blind processing, which will be performed by two separate individuals for statistical analysis of the research results. Participants and teachers will be unblinded when the research is finished by providing a simple report and brochure to the kindergarten.

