#### 3.2.3. Measurement Slots

Participants will be assessed three times: at baseline, the end of the intervention, and the end of the 6-month follow-up. At each time point, we will assess participants’ FMSs, PF, PA, and descriptive data (such as age, sex, weight, height) within one week. The executive plan of FMSs and PF is outlined in Figure 2.

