## 4. Statistical Analysis

### 4.1. Sample Size

The primary outcome variables in this study are FMSs and PF. Before recruitment, a priori power analysis was performed in G*Power 3.1 to calculate the sample size necessary to detect meaningful changes from the baseline to the post-intervention time points in the total raw scores of seven FMSs (i.e., 10-m shuttle-run, hopping, bouncing a ball, jamming coins, kicking, balance beam, and one-leg stand) and seven PF (i.e., balance beam, handgrip, standing long jump, sit-and-reach, 10-m shuttle running, 20-m shuttle running, handgrip strength, and hopping). Using an alpha of 0.05 and a power of 80%, the calculation of the power to detect a pre-post change in these measures was based on the effect sizes reported in a recent systematic review. The expected effect size of the intervention on FMSs and PF was at 1.42 and 0.36 (standardized mean difference, SMD), respectively [51]. With reference to these results, a prudent estimation of the effect size (SMD = 0.36) was used for the calculation. The required sample was calculated to be 70. To account for the clustering effect, this number was then multiplied by a design effect (DE) of 1 + (*m* − 1) × ICC, where *m* is the average cluster size and ICC was estimated at 0.05. With an estimated average class size of 30, at least 150 participants will have to be recruited. Based on previous studies, we presumed a drop-out rate of 15%, implying a minimal sample size of 150/0.85 = 176 children in total. This study takes the class as the cluster of random sampling; the class size in recruited kindergartens is 30–35. Therefore, considering the drop-out rate and special samples (preschool children with developmental retardation or hyperactivity disorder), each experimental group was divided into two classes, implying about 60 children in each group. The total size is 300.

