### 4.4. Data Analysis Plan

Baseline characteristics and unadjusted study outcome measures will be summarized by intervention groups using descriptive statistics and used to assess between-group equivalence at baseline. Prespecified baseline covariates in both primary and secondary outcome analyses will include age, sex, FMSs capacity, PF level, and PA level.

Baseline demographic descriptors and primary and secondary outcome measures will be compared across groups by using analysis of variance (a non-parametric test will be used when the data does not conform with a normal distribution) for continuous variables and the χ^2^ test for categorical variables. The planned descriptive data on measured-point FMSs and PF will be tabulated across the intervention groups and control group. In our primary analysis of the FMSs and PF outcome, we will use mixed model analyses to estimate the differences with their corresponding 95% CIs, comparing the BA, RA, BM, and MA groups with the control group. Time, physical exercise programs (intervention or control groups), and their interaction will be fixed factors. The random effects will be the kindergarten and individual to take into account the clustered data structure.

Multilevel linear regression models will be constructed to assess the effectiveness of the physical exercises on FMSs and PF performance. The baseline data of the outcome variables, assessment points, intervention groups, and any imbalanced covariance will be added to the model along with the kindergartens and PA as random effects. The interaction between physical exercise and FMSs and PF will be tested.

Secondary analyses will investigate the effect of the intervention on other domains using different types of regression analyses, depending on the outcomes. Logistic regressive analyses will be constructed to assess the interference factors. The models will be used to assess the effect of forms of physical exercise, and to explore associations between secondary outcome measures, and will be adjusted for various confounding factors (e.g., sex, PA).

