## 7. Challenges and Limitations

The current protocol has some challenges. First, the participants in this study are 4-–5-year-old preschool children who still largely lack self-control and attentional focus. It will, therefore, be difficult to engage them continuously in the designed physical exercise program. To meet this challenge, the research group will staff each intervention group with two researchers to ensure preschool children’s safety and the intervention quality. Second, the intervention will last for 16 weeks, which will place a great human resource pressure on the PEFP group. We plan to stagger the intervention time of two close kindergartens, and the intervention will be carried out between 8:30 and 11:30 in the morning. In this way, the researchers assigned by the PEFP group can assist more intervention groups within the time allowed.

There are some limitations to this protocol. First, young children are in a rapid period of growth and development; thus, it will be difficult to identify whether natural growth or the exercises intervention contributes to the improvement in children’s FMSs and PF. Like other studies, this protocol will set up a control group in the same school with each intervention group to reduce the confounding impact of natural growth as much as possible. Second, the intervention in this study will last 16 weeks, which seems insufficient to improve FMSs and PF. However, the duration of FMSs or PF interventions in previous studies varied from eight weeks to one academic year or longer [32,41,52,53].

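### The second (multilevel) model for FMSs and PF uses several assessments per child but has no random effect for the child, unlike the primary model

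*Protocol article*

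**What the plan says.** Section 4.4 (Data Analysis Plan) gives two models for the same two primary outcomes.

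- The first is called the primary analysis. Its fixed factors are time, programme and their interaction. On the random part it says: "The random effects will be the kindergarten and individual to take into account the clustered data structure".
- The second is a multilevel linear regression intended to assess how well the programmes work on FMSs and PF. On its terms it says: "The baseline data of the outcome variables, assessment points, intervention groups, and any imbalanced covariance will be added to the model". The same sentence ends by saying that these terms "will be added to the model along with the kindergartens and PA as random effects". It names neither an individual-level effect nor a group-by-time term.

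Section 3.2.3 fixes the number of scores per child: "Participants will be assessed three times: at baseline, the end of the intervention, and the end of the 6-month follow-up". Section 3.2.2 gives the follow-up results an auxiliary role. The only error rate in the document is in section 4.1 ("Using an alpha of 0.05 and a power of 80" per cent), and it is not tied to either model.

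The layout also bears on the size of the effect. Section 2.1 states "Preschoolers recruited from 5 kindergartens will be cluster-randomly allocated to 5 groups", and section 2.3 states "recruited kindergartens as a unit will be randomly assigned to one of five groups". Section 7 says instead that "this protocol will set up a control group in the same school with each intervention group". The checks below cover both layouts.

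**The concern.** A term for assessment points can be estimated only if the data hold more than one assessment. With baseline entered as a covariate, each child then supplies two rows: end of intervention and 6 months. Two scores of the same child stay correlated after baseline adjustment. The second model as listed has nothing to carry that correlation, because kindergarten sits above the child and PA is a measured outcome (section 3.3.2), not a child identifier.

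The second model's standard errors and intervals for programme effects would therefore be wrong. The two models could also disagree on the same outcomes merely because one ignores the repeated measures. This fault is distinct from clustering by class or kindergarten, since it arises even when there is none.

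**Working it through.** **Inputs from the document:** three assessments per child (3.2.3); alpha 0.05, taken as two-sided because the sidedness is not stated (4.1); two classes and about 60 children per arm, ICC 0.05 (4.1); five kindergartens and five arms (2.1).

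**Assumed:** equal correlation r between any two assessments, 0.5 to 0.8. The document gives no value.

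**Step 1. Residual correlation of the two post-baseline scores given baseline.** The partial covariance is r − r² and the partial variance is 1 − r², so ρ = (r − r²)/(1 − r²) = r/(1 + r).
- r = 0.5: ρ = 0.5/1.5 = 0.333
- r = 0.8: ρ = 0.8/1.8 = 0.444

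**Step 2. Variance of the time-averaged arm contrast.** With n children per arm and two rows each, the model takes the variance as 2σ²/(2n). The true value is 2σ²(1 + ρ)/(2n). The ratio is 1 + ρ, that is 1.33 to 1.44. Correct standard errors are √1.33 = 1.15 to √1.44 = 1.20 times those reported.

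**Step 3. Rejection rate at nominal 5%:** P(|Z| > 1.96/√(1 + ρ)).
- ρ = 0 (the plan's own figure): 5.0%
- ρ = 0.333: 1.96/1.155 = 1.70, giving 9.0%
- ρ = 0.444: 1.96/1.202 = 1.63, giving 10.3%
- Wider range: ρ = 0.2 gives 7.4%; ρ = 0.7 gives 13.3%

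**Step 4. A group-by-time contrast, if one were added.** The true variance of a within-child difference is 1 − ρ times the model's. At ρ = 0.333 the rate is P(|Z| > 1.96/√0.667) = 1.6%. At ρ = 0.444 it is P(|Z| > 1.96/√0.556) = 0.9%. The error is then in the conservative direction.

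**Step 5. Simulation in the trial's layout.** Five arms of two classes of 30 children, two post-baseline scores, baseline as covariate, Wald tests of each programme against control, no true effect. Where each kindergarten is one arm, its random effect cannot be separated from the arm, so ordinary least squares was used. PA was left out of the simulated model.

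| Layout | r | Child omitted | Child included |
|---|---|---|---|
| One kindergarten per arm, no clustering | 0.5 | 9.1% | 5.5% |
| One kindergarten per arm, no clustering | 0.8 | 10.5% | 4.8% |
| Arms mixed within five kindergartens, no clustering | 0.5 | 8.9% | 4.7% |
| Arms mixed within five kindergartens, no clustering | 0.8 | 10.0% | 4.7% |
| Arms mixed, kindergarten variance 0.05 | 0.7 | 12.1% | 8.3% |
| Arms mixed, class variance 0.05 | 0.7 | 42.6% | 35.5% |
| One kindergarten per arm, kindergarten variance 0.05 | 0.7 | 59.7% | 53.4% |

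In the last three rows the cluster variance is 0.05 beside a child-level variance of 1 (ICC 0.05/1.05 = 0.048) and enters the post-baseline scores only. The ratios of omitted to included are 12.1/8.3 = 1.5, 42.6/35.5 = 1.2 and 59.7/53.4 = 1.1.

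**The case against.** **Primary inference is already protected.** This stands. The analysis labelled primary includes the individual, and the document ties its 95% intervals against control to that model. A reader might infer that the trial's main tests produce false positives about twice as often as claimed. The text does not support that: the fault is confined to the second model, for which no error rate is stated.

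**The inflation depends on what is tested.** This also stands. It applies to a group effect averaged over both post-baseline assessments. In a simulation of 60 per arm without clustering at r = 0.5 and 0.8, that effect was rejected 8.3% and 10.2% of the time. From a model with group-by-time, the post-test group effect was rejected 5.2% and 5.0% of the time, and the interaction 1.9% and 1.0%. Since follow-up is called auxiliary, a post-test contrast may be what is wanted. But section 4.4 lists no group-by-time term for the second model, so the averaged effect is what its listed terms test. It would be too strong to say that its standard errors are too small for every contrast.

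**PA might act as a child identifier, or a full analysis plan might supply a within-child covariance.** What PA as a random effect means is indeed unclear, and the simulations do not include it. Neither rescue is in the text, though. The article does not leave the random effects open: it lists them, and the list differs from that in the preceding paragraph.

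**Few kindergartens matter.** With several kindergartens per arm (10 or 40 in total), their estimated variance largely absorbed the child variance and rejection was 5.0 to 5.8% with the child omitted. This trial has five kindergartens for five arms, so that protection is absent.

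**Conclusion.** The point holds for the second model only. As written, it treats repeated scores of one child as independent given kindergarten and PA, and so gives wrong standard errors.

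For the time-averaged group effect without clustering, nominal 5% becomes about 9 to 10% if assessments correlate equally at 0.5 to 0.8, and 7 to 13% over residual correlations of 0.2 to 0.7. These correlations are assumptions. A group-by-time contrast would err in the conservative direction.

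An unqualified doubling of the error rate is not supported. At the protocol's ICC of 0.05 the missing term multiplies the error rate by only about 1.1 to 1.5. Nor would adding the term restore 5%: in those three cases the rate stays at 8.3 to 53.4% because of clustering, which is a separate fault. The correction is still worth making, because the two paragraphs contradict each other on the same outcomes.

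**What to change.** In section 4.4, add a random intercept for the individual child to the second model so that it matches the first, or specify an unstructured within-child covariance over assessment points. Alternatively, state that this model analyses one post-baseline assessment, with one row per child.

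The cost is one term in the model statement and somewhat wider intervals for the averaged group effect (about 15 to 20% under the assumed correlations, from step 2). No data collection or trial conduct changes. The clustering fault needs its own remedy.

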## 5. Ethics and Dissemination

An informed consent form will be provided to all participants. Children’s informed consent form will be filled in by their primary guardian, and the preschool administrators will be instructed to sign the corresponding consent. All informed consent forms will be written and recovered and kept by the data manager. Children’s willingness to participate in the study will be determined by communication between the teachers and preschool children. The teacher will introduce the content of the study and the work that the children will need to do, and ask the preschool children if they would like to participate. The intervention will only start after the consent of the preschool children is obtained. Permission for the research protocol was obtained from the ethics review committee of Shanghai University of Sport before participants recruitment.

## 6. Discussion

A panel of researchers has recommended that policies be implemented to increase PA and improve FMSs proficiency and PF levels in preschoolers through school-based initiatives in China. However, the scarcity of physical education lessons specific for preschoolers limits their opportunities to acquire FMSs capacity and meet PF standards. The interventions in this study have several significant points. They use existing school sports facilities (e.g., football, basketball) or even no sport devices (in rhythm activities) to arouse children’s interests to learn and practice motor skills and improve their PF level, without overburdening parents and teachers. The interventions do not require any changes to the curriculum. Overall, the PEFP program represents an attractive strategy for improving FMSs and PF levels among preschool children, providing motor skill-related activities through structured in-school time.

Although there is existing evidence regarding the effectiveness of programs to improve FMSs and PF in healthy preschoolers, this needs to be interpreted prudently as it is based on low-quality evidence, the intervention strategies are combined with other factors (e.g., nutrition, environment), and immediate post-intervention effects without long-term follow-up were assessed [7,36,37,38]. Moreover, in China, except for a policy-driven study on early childhood PF promotion [4], there is a lack of empirical studies concentrating on improving FMSs and PF using school-based physical exercise program interventions. It is, therefore, imperative that the effectiveness of school-based interventions is established to promote FMSs and PF in Chinese children during the vital window in time for FMS acquisition and PF development. In addition, the cohort identified for this school-based physical exercise program intervention will provide possibilities for future research on the influence of early childhood factors on future habitual PA, motor proficiency, and longer-term health outcomes.

## 7. Challenges and Limitations

The current protocol has some challenges. First, the participants in this study are 4-–5-year-old preschool children who still largely lack self-control and attentional focus. It will, therefore, be difficult to engage them continuously in the designed physical exercise program. To meet this challenge, the research group will staff each intervention group with two researchers to ensure preschool children’s safety and the intervention quality. Second, the intervention will last for 16 weeks, which will place a great human resource pressure on the PEFP group. We plan to stagger the intervention time of two close kindergartens, and the intervention will be carried out between 8:30 and 11:30 in the morning. In this way, the researchers assigned by the PEFP group can assist more intervention groups within the time allowed.

There are some limitations to this protocol. First, young children are in a rapid period of growth and development; thus, it will be difficult to identify whether natural growth or the exercises intervention contributes to the improvement in children’s FMSs and PF. Like other studies, this protocol will set up a control group in the same school with each intervention group to reduce the confounding impact of natural growth as much as possible. Second, the intervention in this study will last 16 weeks, which seems insufficient to improve FMSs and PF. However, the duration of FMSs or PF interventions in previous studies varied from eight weeks to one academic year or longer [32,41,52,53].

## 8. Conclusions

This study protocol aims to provide a method to solve the problem of “how to arrange physical exercise and which kind of physical exercise program can promote FMS and PF better in preschool children”.

## Figures and Tables

**Figure 1 ijerph-19-06331-f001:**
[figure not shown]
Design of the PEFP study.

**Figure 2 ijerph-19-06331-f002:**
[figure not shown]
Flow of the assessments of measures in the trial.

**Table 1 ijerph-19-06331-t001:** Description of the contents, specific focus, and time allocation of the four interventions.

Interventions	Specific Focus	Themes	Contents	Lessons Needed
Basic movements	Aims to help preschool children learn and master FMSs, and improve muscular strength, coordination, and sensitivity.	Stable skiers (aiming at stability skills)	Standing and walking	10
		Happy little animals (locomotor skills)	Climbing and running	10
			Jumping	10
		Little ball players (object control skills)	Throwing/catching a ball	6
			Slapping ball	6
			Rolling, kicking, and dribbling	6
Ball games	Enable children to learn and master the basic ball skills, and at the same time promote children’s fitness level.	Rubber ball games	Running/jumping with ball	1
			Rolling pass, throwing, and catching	6
			Slapping and pitching	5
		Basketball games	Slapping basketball	2
			Dribbling	3
			Passing and catching	4
			Throwing, catching, and shooting	4
		Football games	Kicking, stepping over	7
			Dribbling and small-sided games	5
		Tennis games	Tapping	2
			Throwing and catching ball	6
			Hitting fixed ball	3
Rhythmic activities	Develop rhythmic gymnastics, aiming to improve physical control, aerobic fitness, and shaping grace posture.	Animal imitation exercise	Learning basic posture	4
			“I’m a little pacesetter”	12
		Baby warm-up exercise	Basic and jump steps, and body wave	8
		Pizza	“Little swan”	12
		Cheering on	Flower ball cheerleading	12
Multiple activities	Integrates theme activities into physical exercise to cultivate children’s interest and habits regarding regular exercise	Traditional Chinese games	Throw handkerchief games	4
			Beanbags, jumping rope, bench and coin games, etc.	8
		Animal imitation	Hawks Catch chicken, etc.	12
		Role playing and cooperative practice	Pushing cart game, etc.	12
		Military games	Brave little soldiers, etc.	12

**Table 2 ijerph-19-06331-t002:** The Fundamental Movement Skills Tests.

FMS Proficiency	Test	Materials and Site Layouts	Directions	Performance Records	Cautions
Locomotor skills	10-m shuttle run	Materials: flexible rulers, marking tap, poles, and stopwatch Site layouts: two parallel lines 10 m (m) apart will be marked on the floor using marking tap	Child runs concurrently with an audio signal, then runs back once reaching the turning line	The result will be recorded in seconds	Stay clear of the starting and turning line
Hopping	Hopping	Materials: tape measure, marking taps, stopwatch, and beanbag 10 cm long, 5 cm wide, and 5 cm high Site layouts: 10 parallel lines 0.5 m apart, on which a piece of beanbag will be placed	Child stands behind the starting line and hops with close feet continuously as soon as he/she hears the audio signal, and until he/she hops over the last beanbag	The result will be recorded in seconds	Repeat the test if the child hops over the beanbag with one leg, steps onto the beanbag, or kicks the beanbag from where it is two times
Object control skills	Bouncing a ball	Materials: soft balls and stopwatch. Site layouts: 1 m × 1 m square	Child dribbles the ball with one hand 8 times (as ball bouncing higher over his/her knees, it is counted as one)	The result will be recorded in seconds	Push balls with fingertips, not a slap
Object control skills	Jamming coins	Materials: 8 coins, a box with slot on the upper side and stopwatch	Child stuffs 8 coins into the box through the slot with the dominant hand	The result will be recorded in seconds	
Object control skills	Kicking	Materials: Sand-filled solid balls and sign barrels Site layout: 3 m, one sign barrel every 1.5 m	Child kicks the solid ball from one side to the other side with the arch of their foot, bypassing the 1.5-m sign barrel, and the route is in the shape of “C”	The result will be recorded in seconds	Repeat the test if child kicking the ball not with arch of foot
Stability skills	Dynamic balance (Balance beam)	Materials: balance beam (3 m long, 10 cm wide, and 30 cm high) with two platforms (20 cm long, 20 cm wide and 30 cm high) attached to both ends, and a stopwatch	Child walks consecutively forward on the balance beam, until one of the feet touch the platform on the other side	The result will be recorded in seconds	1. Repeat the test if the child falls off the beam 2. Testers should protect the child from harm during the test
Stability skills	Static balance (One-leg stand)	Material: stopwatch	Child stands on one foot with the supporting leg on the floor and the free leg flexed at the knees, maintaining the balance posture until the required posture cannot be maintained	The result will be recorded in seconds	

**Table 3 ijerph-19-06331-t003:** Physical Fitness Tests.

PF Proficiency	Test	Materials and Site Layouts	Directions	Performance Criteria	Cautions
Balance	Balance beam	As aforementioned in Table 2.			
Upper Limbs Strength	Handgrip	Materials: grip meter special for young children (TKK5825 TKK, in TAKEI, Japan).	Child squeezes gradually and continuously for at least 2 s or 3 s with one hand.	The result will be recorded in kilograms.	Testers adjust the grip meter for the optimal span for the child before the test.
Lower limbs strength	Standing Long Jump	Materials: tape measure, marking taps. Site Layout: a take-off line marked on the surface with taps.	Child will be instructed to stand with feet at shoulder width, and toes just behind the take-off line; then, child bends knees while swinging both arms, and pushes off vigorously and jumps as far as possible.	The reported distance is measured from the take-off line to the point where the back of the heel nearest to the take-off line lands on the ground. The result will be recorded in meters.	
Flexibility	Sit-and-reach	Material: sit-and-reach device.	Child will be instructed to take off their shoes, sit on the floor with legs fully extended, and press his/her feet against the base of the device. With arms fully extended and hands overlapped with palms down, child reaches as far forward as possible and pauses for 2 s.	The result will be recorded in centimeters.	Child will be required to stretch his/her lower back, hamstrings, and calves before the test.
Agility	10-m shuttle-run	As aforementioned in Table 2.			
Coordination	Hopping	As aforementioned in Table 2.			
Cardiorespiratory fitness	20-m shuttle-run	Materials: flexible rulers, marking tap, poles, and stopwatch. Site layout: two parallel lines 20 m apart will be marked on the floor using marking tap.	Child will be instructed to run progressively to exhaustion from one line to another 20 m apart, changing direction at the pace set by an audio signal that increases progressively.	The test ends when the child fails to reach the end lines concurrent with the audio signal on two consecutive occasions or when the child stops because of exhaustion.	Testers will be continually encouraging participants so that they give their best performance. Child performs a test no longer than 8–10 min.

